## Methods/Design

### Study design and setting

This is a 6.5-month randomised crossover controlled clinical trial (RCT) in which adults aged 40–60 years with diagnosed pre-diabetes will be enrolled. Potential study participants will be identified from General Practice (GP) clinics throughout South Gippsland, Victoria. The study design is presented in Figure 1.

**Figure 1 F1:**
[figure not shown]
Trial protocol.

### Inclusion criteria

Individuals aged between 40–60 years and diagnosed with prediabetes (Impaired Fasting Glucose or Impaired Glucose Tolerance) within the previous 12 months. Diagnosis will have been made at each individual’s local GP clinic after undertaking an Oral Glucose Tolerance Test (OGTT). Prediabetes was defined as a fasting plasma glucose concentration ≥ 6.1 and < 7.0 mmol/L followed by a 2-hour post glucose load glucose concentration < 7.8 mmol/L, or a fasting plasma glucose < 7.0 mmol/L followed by a 2-hour post glucose load glucose concentration ≥ 7.8 and < 11.1 mmol/L [38].

### Exclusion criteria

Individuals previously diagnosed with type 1, type 2 diabetes or impaired renal function (eGFR <90 mL/min/1.73 m^2^), individuals with known gastrointestinal pathology (coeliac disease, inflammatory bowel disease), pregnant women, smokers, individuals who have taken antibiotics, dietary prebiotic or probiotic nutritional supplements within the previous three months, individuals taking aspirin or Vitamin B, individuals who have made major dietary or lifestyle changes in the previous three months, individuals who are unwilling to provide blood, urine and stool samples or are unable to attend their local pathology collection centre.

### Ethics

The trial has received ethical approval from the Monash University Human Research Ethics Committee.

### Sample size calculation

The minimum difference we wish to detect is 0.4 micromol/L serum CML (20% reduction in CML), with a standard deviation of 0.4 [39] with 5% Significance and 80% Power. This calculates as a total sample size of 18 individuals, plus 12 individuals to allow for withdrawals = 30 subjects required. Epidemiological studies have demonstrated a positive correlation between serum CML and all-cause and cardiovascular mortality, cardiovascular disease, glucose intolerance, impaired insulin secretion, renal impairment and diabetic vascular complications [40,41]. A 0.4 micromol/L increase in serum CML concentration represented a 68% increased risk for all-cause mortality over seven years in a large prospective cohort study [42].

### Baseline assessment

The study timeline is presented in Figure 2. Following recruitment and screening, consenting participants will undergo a baseline assessment at their local GP clinic. The baseline assessment will be undertaken by the research dietitian, who will collect demographic details, medical and social history (living situation, marital status, current occupation), physical activity questionnaire, dietary intake assessment, anthropometric measurements including Body Mass Index (BMI) and waist circumference. Participants will also be instructed to attend the local pathology centre to provide a stool sample, 24-hour urine collection, and have blood taken for analysis.

**Figure 2 F2:**
[figure not shown]
Study flowchart.

### Randomisation

Randomisation of participants to intervention/placebo sequence will be completed by a local pharmacist using a permuted-block randomisation stratified by gender via the web site http://www.randomization.com. The pharmacist will distribute the experimental and placebo nutritional supplements to participants in the appropriate sequence. Other than provision of supplements, the pharmacist will have no contact with study participants or involvement in data collection or analysis. Dietary supplements will be provided in sealed opaque packages which will be weighed at the conclusion of the study in order to assess compliance. The supplements will be packaged off-site by an external pharmaceutical packaging agency. Each package will contain a participant’s study identification number and will be labelled as either Supplement 1 or Supplement 2 corresponding to the first and second intervention periods. This will ensure all investigators and participants are blinded to the treatment. Blinding will cease only after statistical analysis of the data has been completed.

### Intervention

Participants will be randomly assigned to receive either 10 g of chicory-derived inulin/oligofructose powder (kindly provided by Beneo-Orafti Active Food Ingredients, Belgium) (intervention) or 10 g of maltodextrin powder (placebo) daily. Previous studies have demonstrated the bifidogenic effect of daily consumption of 5 g and 8 g dietary inulin supplements [43]. The inulin and maltodextrin powders to be consumed are both tasteless and can be mixed into hot or cold liquids or semi-solid foods. Participants will be instructed how to incorporate their supplement into their usual diet, and advised to gradually increase their dose over ten successive days until the target dose is reached. This stepped escalation in supplement dose aims to minimise gastrointestinal discomfort for participants, as a sudden increase in dietary prebiotic intake may result in increased stool frequency, abdominal bloating and flatulence until the bowel adapts to the increased fibre intake [44]. Written instructions will also be provided. Participants will be advised to consume each dietary supplement daily for 90 days, and otherwise maintain their usual dietary intake and level of physical activity. Gastrointestinal tolerance to the dietary supplements will be indicated by each study participant using a visual analogue scale as described below.

### Follow up visits

Visits to the GP clinic will be scheduled for each participant at the conclusion of both Intervention 1 and Intervention 2 treatment periods, in order to provide follow-up data. Information collected will include anthropometric measurements, dietary intake assessment and physical activity assessment. Each participant will complete a self-administered questionnaire designed to assess gastrointestinal tolerance to the dietary supplement. Completed questionnaires will be placed into sealed opaque envelopes in order to maintain blinding of the researcher collecting data during the follow-up visits. Participants will also be instructed to attend the local pathology centre to provide urine and stool samples, and have blood taken for analysis.

### Safety considerations

All adverse events will be documented.

### Outcome measurements

The primary outcome of interest is the difference in serum AGE and AGE-precursor concentration (measured as CML and MG respectively) between experimental and control treatments. Secondary outcomes include HbA1c, insulin resistance (measured indirectly by homeostasis model assessment), antioxidant capacity (reduced glutathione), markers of oxidative stress on lipid molecules (urinary 8-isoprostanes), inflammatory biomarkers (serum IL-6, high sensitivity C-reactive protein, MCP-1, sRAGE), adhesion molecules (E-selectin), gut barrier integrity (TLR4), 24-hour urine and faecal CML and MG concentrations, faecal bacterial composition (*Bifidobacterium* spp., *Lactobacillus* spp., *Roseburia* spp., *Faecalibacterium prausnitzii* and *Akkermansia muciniphila*) and faecal short chain fatty acid concentrations. Lipid levels (serum total cholesterol, LDL, HDL, TG) and blood pressure will also be measured. Anthropometric measurements including BMI and waist circumference will be collected, in addition to comprehensive dietary and lifestyle data. Gastrointestinal side-effects will be assessed using a visual analogue scale adapted from Lecerf *et al.*[45]. The scale rates nine items including flatulence, bloating, rumbling, abdominal cramps, a global digestive tolerance score calculated from the five previous items, stool consistency, stool frequency and general well-being through disturbances in usual and professional activities as well as disturbances in personal and social activities. Items are scored on a 10 cm linear scale.

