**Methods/Design:**

Thirty adults with pre-diabetes (Impaired Glucose Tolerance or Impaired Fasting Glucose) aged between 40–60 years will be randomly assigned to receive either 10 grams of prebiotic (inulin/oligofructose) daily or 10 grams placebo (maltodextrin) daily for 12 weeks. After a 2-week washout period, study subjects will crossover to receive the alternative dietary treatment for 12 weeks. The primary outcome is the difference in markers of the advanced glycation pathway carboxymethyllysine (CML) and methylglyoxal (MG) between experimental and control treatments. Secondary outcomes include HbA_1c_, insulin sensitivity, lipid levels, blood pressure, serum glutathione, adiponectin, IL-6, E-selectin, myeloperoxidase, C-reactive protein, Toll-like Receptor 4 (TLR4), soluble receptor for AGE (sRAGE), urinary 8-isoprostanes, faecal bacterial composition and short chain fatty acid profile. Anthropometric measures including BMI and waist circumference will be collected in addition to comprehensive dietary and lifestyle data.

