### Statistical analysis

Outcome analyses will be undertaken on an intention-to-treat basis. Data will be presented as means ± SD. The Kolmogorov-Smirnov goodness-of-fit test will be used to test for normal distribution, and data not normally distributed will be log-transformed. Correlation analyses will be performed using the Pearson correlation coefficient. Significance of changes during the study will be assessed by comparing change of means between placebo and prebiotic treatment periods by paired sample t-tests. Trial data will be analysed using a linear mixed model design based on repeated measures to account for fixed factors such as treatment sequence (inulin – placebo vs placebo - inulin) and treatment period (intervention 1 vs intervention 2) in addition to participants as a random factor. Significant differences will be defined as a value of P < 0.05 based on two-sided tests. Any differences in physical activity levels, anthropometry, energy or nutrient intake during the course of the trial will be identified using ANOVA. Gastrointestinal symptom data obtained by visual analogue scale will be analysed using the Wilcoxon signed rank test. Effect sizes including 95% confidence intervals will be calculated for all significant outcomes. Data analysis will be performed using SPSS 20.0 software (SPSS, Chicago, IL).

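### Serum CML and MG are both named primary with no rule for success, yet the 5% significance and 80% power were set for CML alone

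*Protocol article*

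**What the plan says.** The abstract (Methods/Design) and the Outcome measurements section agree that two markers are primary. The abstract says: "The primary outcome is the difference in markers of the advanced glycation pathway carboxymethyllysine (CML) and methylglyoxal (MG) between experimental and control treatments". The Outcome measurements section says: "The primary outcome of interest is the difference in serum AGE and AGE-precursor concentration (measured as CML and MG respectively". That section lists the urinary and faecal concentrations of both markers as secondary, so the primary pair is the serum measurements. Under Laboratory investigations, CML is measured by competitive ELISA and MG by HPLC; nothing combines them into one score.

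The Statistical analysis section gives one decision rule for everything: "Significant differences will be defined as a value of P < 0.05 based on two-sided tests". It then says: "Effect sizes including 95% confidence intervals will be calculated for all significant outcomes". Significance is therefore declared outcome by outcome. The section states no testing order, no division of the 5% and no requirement that both markers succeed.

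The Sample size calculation section considers CML only: "The minimum difference we wish to detect is 0.4 micromol/L serum CML (20% reduction in CML), with a standard deviation of 0.4 [39". The error rate and power are attached to that one marker, at an unsplit 5% and at 80%. The section concludes: "This calculates as a total sample size of 18 individuals, plus 12 individuals to allow for withdrawals = 30 subjects required". It gives no difference, SD or power for MG.

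**The concern.** The article makes three positive choices: two primary outcomes, a full 0.05 for each test, and a sample size that spends the full 5% and 80% on one of the two. They do not fit together under any rule for success.

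- If either marker may succeed, 5% is not the error rate of the primary claim.
- If both must succeed, 80% is not the power of that claim.
- If CML alone decides, MG should not be called primary.

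At stake is how the trial may be reported. As written, a null result on CML with P = 0.04 on MG could be presented as a positive primary result, on a marker the trial was never sized for and at an error rate stated nowhere.

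**Working it through.** **Inputs from the article.** CML difference 0.4 micromol/L, SD 0.4, 5% significance, 80% power, 18 evaluable plus 12 for withdrawals (Sample size calculation); two-sided 0.05 and paired t-tests (Statistical analysis). **Not in the article:** the type of SD, the correlation between the CML and MG tests, and any MG effect or SD.

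**1. Reproducing the 18.** Read 0.4 as the SD of a single measurement with zero within-person correlation.

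- SD of the paired difference = 0.4 × √2 = 0.566.
- Noncentrality at n = 18 = 0.4 / (0.566/√18) = 3.00.
- Power of the two-sided paired t-test at 0.05 (noncentral t, 17 df) = 80.7%, and 18 is the smallest n that reaches 80%.

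So the stated 18 reproduces, for CML alone at the full 5%. If 0.4 were instead the SD of the difference, the t-test would need only 10. The allowance for withdrawals is consistent: 18 / (1 − 12/30) = 30.

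**2. Either marker counts.** With one test per marker, both null hypotheses true and correlation ρ between the test statistics, the error is 1 − P(|Z₁| < 1.96 and |Z₂| < 1.96).

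- Upper bound for any ρ: 0.05 + 0.05 = 10%.
- ρ = 0: 1 − 0.95² = 9.75%.
- ρ = 0.2: 9.6%.
- ρ = 0.5: 9.1%.
- ρ = 0.7: 8.3%.
- ρ = 0.9: 7.0%.

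The values of ρ are an assumed range.

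**3. Both markers must be significant.** With both nulls true, the error is 0.05 + 0.05 minus the figure in step 2: 0.25% at ρ = 0 and 3.0% at ρ = 0.9. It cannot exceed 5% even if one marker truly responds, because the other must still pass its own 5% test. Power for the pair cannot exceed the power for CML. With 18 completers, the planned 80% is therefore a ceiling, and how far below it the trial sits depends on MG figures the article does not give.

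**4. Cost of the possible repairs for CML.**

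- Fixed order, CML first at 0.05: power unchanged (80.7% at 18 completers with SD of the difference 0.566), overall error 5%.
- CML tested at 0.025, which is the Bonferroni level and the worst case for CML under Holm: with SD of the difference 0.566, power at 18 completers is 70.3%, 22 completers are needed for 80%, and power is 92.8% if all 30 complete. Twenty-two completers remain if no more than 8 of 30 (27%) are lost.
- The same test with SD of the difference 0.4 (within-person correlation 0.5): power at 18 completers is 95.3%.

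**The case against.** The strongest reply is that the article nowhere adopts an either-marker rule. It joins the two markers with a simple conjunction as one primary outcome, which also fits a both-markers reading with no inflation at all. This stands. A reader might infer that the primary claim has a false-positive rate near 10%; the text supports that only conditionally, and 9.75% lies near the top of the range. The article classes MG as a precursor of AGEs, so some positive correlation is plausible and would lower the rate.

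A second reply is that testing order and multiplicity are often left to a statistical analysis plan, which is not shown. This stands in part: missing detail alone would be no finding. But the article itself fixes two primaries, an unsplit 0.05 and a one-marker sample size, and those statements conflict whatever a later plan adds.

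Three further inferences are tempting and not supported:

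- A definite power for the both-markers rule. It would need an assumed power for MG, and the article gives no basis for one.
- A fixed power loss under Holm. The 70% and 95% in the working differ only in how the SD is read. The first reading reproduces 18, but the article does not say which is meant.
- A demand to adjust the secondary outcomes. Testing outcomes labelled secondary without adjustment is ordinary practice, and the article makes no confirmatory claim for them.

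Finally, this is a small biomarker trial that describes its endpoints as surrogates and says longer studies must confirm the results. That weighs on severity, and the CML test taken alone remains a 5% test sized as stated.

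**Conclusion.** The point holds in conditional form. The stated 5% and 80% describe the primary claim only if CML alone decides, and the abstract and Outcome measurements section say otherwise. If either marker suffices, the false-positive rate is up to about 10% instead of 5%; if both are required, error is controlled but power is unknown. The first figure rests on one test per marker, both nulls true and an assumed correlation. The second conclusion needs no assumption beyond the absence of MG inputs. The sample size of 18 is not itself wrong. This should be fixed, but it does not invalidate the trial.

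**What to change.** Before unblinding, state in the Outcome measurements and Statistical analysis sections that serum CML, the outcome on which the trial was sized, is tested first at two-sided 0.05, and that MG is tested at two-sided 0.05 and claimed only if CML is significant. State in the Sample size calculation section that the 80% power refers to CML. The order must be set without sight of treatment results; chosen afterwards, it no longer controls the error rate.

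Cost: a few sentences, and a short amendment to the registered outcome wording where it matches the article. MG can no longer be claimed on its own. CML loses no power and the 18 stands.

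Alternative: Holm across the two markers, if the investigators want MG to be claimable without CML. Its worst-case cost to CML power is the 0.025 calculation in the working; the type of SD should be stated first, because that cost depends on it.

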## Data collection

### Dietary intake

An experienced research dietitian will obtain a comprehensive dietary history from each study participant at baseline and at the completion of each intervention period. A dietary history is a structured interview method consisting of questions regarding habitual food intake. It involves a 24-hour diet recall followed by a food frequency questionnaire to clarify information about usual consumption over the previous month. Usual portion sizes will be obtained in household measures and with the use of photographic aids. The dietitian will review the dietary history with each participant, probing for details on portion sizes and cooking methods in order to improve data accuracy. Dietary AGE content will be estimated from an open source database which lists the AGE concentration of foods using validated analytical techniques [46]. Dietary macro and micronutrient intakes will be estimated using the Foodworks nutrient software program (Xyris Software, NSW, Australia). Each participant will also be randomly contacted by telephone during the study and asked to provide a 24-hour diet recall, and changes in urinary urea excretion will be monitored in order to validate the dietary history data collected [47]. Physical activity will be estimated by asking participants to complete the International Physical Activity Questionnaire (Short Form) prior to and at the completion of experimental and placebo intervention periods [48].

### Anthropometry

Body weight will be measured in participants wearing light clothes without shoes using a digital scale (Seca, Germany) to the nearest 0.1 kg. Height will be measured using a portable stadiometer (Seca, Germany) to the nearest 0.1 cm. BMI is calculated by dividing weight (kg) per height (m) square. Waist circumference will be measured at the midpoint of the lowest rib and iliac crest using a measuring tape to the nearest 0.1 cm. Body composition (total body water, fat mass, fat-free mass) will be determined using Bioelectrical Impedance Analysis (BodyStat-1500, Bodystat, Douglas, Isle of Man, United Kingdom). Ambulatory blood pressure will be measured using an electronic blood pressure machine (Omron Corporation, Kyoto, Japan), with subjects at rest in a seated position. All anthropometric measurements will be conducted in duplicate, with the mean measurement recorded.

### Laboratory investigations

Biological samples will be collected at baseline and at completion of each three-month supplement intervention period and stored at −80°C immediately after collection. Twenty ml of fasting venous blood will be collected from each participant by phlebotomy into a sodium fluoride EDTA tube, a heparin-lined vacuum tube and a clean glass test tube. Twenty-four hour urine collections and morning stool samples will be collected in sterile containers.

Serum, urinary and faecal CML will be measured using a competitive ELISA (AGE-CML ELISA, Microcoat, Penzberg, Germany) [49]. This assay has been validated [50], is specific, and shows no cross-reactivity with other compounds [49]. The within assay and between-assay coefficient of variation are both less than 5%, respectively. Methylglyoxal will be measured by HPLC. Serum total cholesterol and triglyceride concentrations will be determined by enzymatic colorimetric assay (Technicon Instruments, Ltd., New York, N.Y., USA), while HDL cholesterol will be determined enzymatically in the supernatant after precipitation of other lipoproteins with dextran sulphate-magnesium. LDL-cholesterol will be calculated using the Friedewald formula. Plasma glucose levels will be determined by using an automated glucose oxidase method (Glucose analyser 2, Beckman Instruments, Fullerton, California). Insulin will be measured by enzymatic colorimetry (WAKO Pure-Chemical Industries, Osaka, Japan). Insulin Resistance (IR) will be estimated by the homeostasis model assessment (HOMA) index as [FI × (fasting glucose/22.5)], where FI is insulin in microunits per millilitre and fasting glucose is in millimoles per litre [51,52]. HbA1c will be measured by autoanalyser (Roche Diagnostics, Mannheim, Germany). Plasma IL-6, MCP-1, E-selectin, hsCRP, TLR4, glutathione (GSH), and myeloperoxidase will be measured by commercial ELISA kits (Biosource International, Camarillo, CA, USA). Urine 8-isoprostanes will be measured by ELISA (Oxford Biomedical Research, MI, USA).

Stool samples will be homogenised in a blender and stored at −20°C for SCFA analysis. Samples will be thawed and 5 g aliquots placed in Centriprep fluid concentrators, MWCO 30,000 kDa (Amicon Inc., Beverly, MA, USA). Samples will be centrifuged for 30 minutes at 1000 × g, room temperature and supernatants placed in 15 ml polypropylene tubes. 0.3 ml of 25% m-phosphoric acid will be added to each tube, samples will be vortexed and incubated at room temperature for 25 minutes. Samples will be centrifuged at 5000 × g for 15 minutes at room temperature. Supernatants will be decanted and frozen overnight. The following day, samples will be thawed and the pH of each sample adjusted to 6.5 using 4 N KOH. Oxalic acid will be added at a final concentration of 0.03% and SCFA concentrations determined by gas chromatography with use of a Hewlett-Packard 5880A gas chromatograph (Hewlett Packard, Palo Alto, CA, USA) containing an 80/120 Carbopack B-DA/4% Carbowax 20 M column (Supelco Inc., Bellefonte, PA, USA).

Quantitative Real-time PCR will be used to determine faecal concentrations of *Bifidobacterium* spp., *Lactobacillus* spp., *Roseburia* spp., *Faecalbacterium prausnitzii* and *Akkermansia muciniphila*. The primers used will be based on the following 16S rRNA gene sequences: *Bifidobacterium* spp: F-CTCCTGGAAACGGGTGG and R-GGTGTTCTTCCCGATATCTACA [53], *Lactobacillus* spp: F-AGCAGTAGGGAATCTTCCA and R-CACCGCTACACATGGAG [54], *Roseburia* spp: F-CGKACTAGAGTGTCGGAGG and R-GTCATCTAGAGTGTCGGAGG [55], *Faecalbacterium prausnitzii*: F-GGAGGAAGAAGGTCTTCGG and R-AATTCCGCCTACCTCTGCACT [56], and *Akkermansia muciniphila:* F-CAGCACGTGAAGGTGGGGAC and R-CCTTGCGGTTGGCTTCAGAT [57]. PCR amplification and detection will be achieved with an ABI 7300 Real-time PCR system (Applied Biosystems, Foster City, CA, USA) using Mighty Amp for Real-time (SYBR Plus) and Rox Reference Dye (Invitrogen, Carlsbad, CA, USA). Each assay will be performed in duplicate in the same run. The cycle threshold of each sample will then be compared with a standard curve (performed in duplicate) made by diluting genomic DNA (tenfold serial dilution). Prior to isolating the DNA, the cell counts will be determined in culture and expressed as “colony forming units” (CFU). Data will be expressed as log CFU/g of faeces.

